### Assignment of interventions: blinding

#### Who will be blinded {17a}

All trial staff including the care providers will be blinded except the site pharmacist.

#### Procedure for unblinding if needed {17b}

If, in the opinion of the local clinician, it is crucial for clinical care to unblind treatment (for instance because of a severe reaction that may have other causes that require investigation), the documented request will be discussed with the site principal investigator (PI) and then the chief investigator (CI). The protocol for emergency unblinding (described in an ‘Emergency unblinding’ SOP) includes both secure access to the allocation from the study pharmacist, for the patient’s clinical management team, and clear record keeping of the event in question.

### Data collection and management

#### Plans for assessment and collection of outcomes {18a}

After the written informed consent is obtained from each participant, baseline, outcome and other trial data will be collected on the paper source document and then entered into the database via an electronic case report form (eCRF). All information from a performed visit will be entered into the eCRF in a timely manner (e.g. within 1 week of data generation). Source documents include, but are not limited to, hospital records (from which medical history and previous and concurrent medication may be summarised into the CRF), clinical and office charts, laboratory and pharmacy records, radiographs and correspondence. CRF entries will be considered source data if the CRF is the site of the original recording.

#### Plans to promote participant retention and complete follow-up {18b}

Where possible, study follow-up visits are timed to coincide with routine clinical appointments. Allowable windows are ±2 days for weekly follow-up visits and ± 1 month for 4-monthly follow-up visits to provide some degree of flexibility. Participants who miss a visit will be contacted by phone for a maximum of three times after which a maximum of three home visits can be conducted. All contact attempts will be recorded.

### Data management {19}

All data will be entered by site staff into a cloud-based data management system, CASTOR (https://www.castoredc.com). CASTOR is secured according to the most recent standards and is certified for ISO 27001 (Standards for Information Security Assurance). The data system includes password protection and internal quality checks, such as automatic range checks, to identify data that appear inconsistent, incomplete or inaccurate. Access to data will be determined by the study administrator and can be granted per person per institute.

### Confidentiality {27}

Data will be collected and stored in accordance with GCP and with the EU General Data Protection Regulations.

### Plans for collection, laboratory evaluation and storage of biological specimens for genetic or molecular analysis in this trial/future use {33}

Various biological samples will be collected, evaluated and stored for future laboratory sub-studies as indicated in Table 3.

### Statistical methods

A summary of the statistical approaches is provided here. Full details are outlined in the Statistical Analysis Plan. All efficacy comparisons test hypotheses of the superiority of RPT/INH against placebo, with a significance level of 0.025 (one-sided).

#### Analysis populations

The intention-to-treat (ITT) population, defined as all randomised patients, regardless of whether they are ineligible, withdraw, do not comply with the protocol or do not receive any study treatment, will be the main analysis population. Patients will be analysed according to the intervention they were randomised to receive. The per-protocol population excludes patients who did not complete planned treatment (complete treatment is defined as at least 11 doses of study treatment over no more than 16 weeks) and patients with major protocol violations (eligibility violations, follow-up outside allowable windows and incomplete TB outcome assessment).

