#### Criteria for discontinuing or modifying allocated interventions {11b}

Trial participants may choose to discontinue the trial treatment at any time without penalty or loss of benefits to which they are otherwise entitled. Although the participant is not required to give a reason for discontinuing their trial treatment, a reasonable effort will be made to establish this reason while fully respecting the participant’s rights. Participants who discontinue treatment should remain in the trial for the purpose of follow-up and data analysis (unless the participant withdraws their consent for follow-up).

The following criteria may result in treatment interruption:
Occurrence of an adverse eventRequirement for prohibited medicationsPregnancy or breastfeeding (permanent discontinuation)Diagnosed with TB by a clinician, warranting anti-TB treatment (permanent discontinuation)Request by the participant to stop treatmentIntercurrent illness or change in the participant’s condition that justifies the discontinuation of treatment in the treating physician’s opinion and after discussion with the site PIInadequate compliance with the protocol treatment in the judgement of the treating physician

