#### Strategies to improve adherence to interventions {11c}

Study drugs will be given orally in the outpatient clinic under the direct supervision of the research staff. Compliance will be confirmed through a review of the medication charts and directly observed administration. Furthermore, participants who miss a visit will be contacted by phone for a maximum of three times after which a maximum of three home visits can be conducted. All contact attempts will be recorded. Participants who miss one or more doses of study treatment can restart within 4 weeks of their last dose and complete their treatment. Subsequent follow-up will be based on their last treatment date.

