### Outcomes {12}

#### Primary outcome

The primary outcome is the occurrence of probable or definite TB disease. Definite TB disease will be diagnosed by a culture or Xpert positive result for *M. tuberculosis.* Probable TB will be diagnosed according to an algorithm that takes into account symptoms, chest x-ray reading, sputum smear, histology and verbal autopsy results (see Table 1).

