**Blood samples for future laboratory studies**																					
Blood for DNA/RNA/plasma in *n* = 6000 screened and upon TB diagnosis during follow-up (*n* = ~ 100–150)	X															X					
Follow-up Quantiferon Gold Plus in trial (*n* = ~ 600) participants															X						
Blood for DNA/RNA/plasma in trial (*n* = 3000) participants during follow-up															X		X				

^a^Questionnaire (age and sex, education, socioeconomic status, use of alcohol, smoking) and clinical assessment (DM history, DM management, DM complications, TB history, history of exposure to TB, TB treatment, family history of DM and TB, BMI, blood pressure, waist-hip circumference)

^b^Investigations for TB may be carried out at any time if patients present with symptoms of TB. During the screening phase, only Xpert will be used to diagnose TB; the sample will be stored for culture. Investigations for extra-pulmonary TB will be carried out if clinically indicated according to the specified SOP ‘Handling suspected extra-pulmonary TB’

^c^Total bilirubin, AST (SGOT), ALP and Cr

^d^At baseline, all signs and symptoms that occurred within 30 days before entry will be recorded

^e^Doses must be given at least 72 h apart. Adherence will be recorded each week until the completion of treatment (or discontinuation of treatment). Allowable windows are ±2 days for weekly follow-up visits during the 12 weeks of drug administration

^f^Measured using the EQ-5D-5L as part of the cost-effectiveness sub-study

^g^Telephonic follow-up assessment schedule at months 5, 7,10, 14, 18 and 22

Lipid profile (cholesterol, triglycerides, LDL, HDL)

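### As worded, the per-protocol exclusions clash with the restart rule and 16-week limit, drop TB cases treated before dose 11, and select on later follow-up

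*Protocol article*

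**What the plan says.** All references are to the Protocol article.

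- **Analysis populations.** ITT is the main population. The per-protocol population leaves out participants who did not complete treatment, where "complete treatment is defined as at least 11 doses of study treatment over no more than 16 weeks". It also leaves out those with "major protocol violations (eligibility violations, follow-up outside allowable windows and incomplete TB outcome assessment".
- **Section {20c}.** Per-protocol is a secondary analysis of the primary endpoint, limited to those who took study drug as planned.
- **Visit windows.** Section {18b}: "Allowable windows are ±2 days for weekly follow-up visits and ± 1 month for 4-monthly follow-up visits". Table 3, footnote e: "Allowable windows are ±2 days for weekly follow-up visits during the 12 weeks of drug administration".
- **Restart, section {11c}.** "Participants who miss one or more doses of study treatment can restart within 4 weeks of their last dose and complete their treatment". It adds: "Subsequent follow-up will be based on their last treatment date".
- **Stopping study drug, section {11b}.** One listed criterion is "Diagnosed with TB by a clinician, warranting anti-TB treatment (permanent discontinuation").
- **Endpoint.** "The primary outcome is the occurrence of probable or definite TB disease". It is analysed as an incidence rate ratio by Poisson regression (section {20a}).

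**The concern.** Three features of the definition work against the analysis it is meant to serve.

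1. **Internal conflict.** The dosing criterion tolerates delay up to 16 weeks and section {11c} lets people restart after missed doses. The list of major violations then appears to exclude the same people for being off the weekly schedule.
2. **Loss of endpoint events.** A participant diagnosed and treated for TB before dose 11 has to stop study drug, so becomes a non-completer and leaves the set. Those who remain contribute the same weeks as event-free time if the clock starts at randomisation.
3. **Selection on later follow-up.** A late visit or an incomplete assessment removes the whole participant rather than ending that person's follow-up. Someone diagnosed early has fewer scheduled visits to miss than someone who stays event-free, so retention depends on the outcome.

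At stake is how far the planned analysis of adherent participants can be trusted. Adverse events are a listed reason for interrupting treatment, so completion could differ between arms.

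**Working it through.** **Design figures first.** Inputs from Sample size {14}: 22.5 cases/1000/year on control, RR 0.5, 3000 randomised, 10% loss, 90% power, one-sided 0.025, 1:1. The 2-year risks are 0.045 and 0.0225. The two-proportion formula (pooled variance, no continuity correction) gives 2704 in total; 2704/0.90 = 3005 after rounding up, against 3000 stated. Power with 1350 per arm is 0.900. All nine cells of Table 4 reproduce exactly. The planning rates can therefore be used as they stand.

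**Windows against the 16-week limit.** Table 3 dispenses drug from Day 0 to Week 11, so there are 12 doses and 11 intervals.

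- Every visit within ±2 days of a fixed schedule: the last dose falls by day 11 × 7 + 2 = 79 (11.3 weeks).
- Every interval stretched to 9 days: 11 × 9 = day 99 (14.1 weeks).
- Limit: 16 × 7 = day 112.
- One 28-day gap followed by a restart, the other ten intervals on time: 28 + 10 × 7 = day 98 (14.0 weeks), with all 12 doses taken.

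The last participant completes inside 16 weeks but misses the three weekly visits at 7, 14 and 21 days into the gap. That person satisfies the dosing criterion and, read literally, fails the window criterion. Nobody reaches day 112 without a missed or late visit.

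**TB before dose 11.** Dose 11 falls at Week 10. Assume a constant rate, and that every endpoint case in this period is also diagnosed and treated by a clinician.

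- Placebo events over 24 months: 0.0225 × 2 × 1350 = 60.75. In the first 10 weeks: 60.75 × 10/104 = 5.8.
- 3HP at RR 0.5: 30.375 × 10/104 = 2.9.
- Share: 10/104 = 9.6%.
- With 1500 per arm and 52.18 weeks per year: 1500 × 0.0225 × 10/52.18 = 6.5 placebo, and half of that, 3.2, on 3HP.

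**Effect on the rates, if person-time starts at randomisation.** Placebo: (60.75 − 5.84)/2700 person-years = 20.3/1000, against 22.5. 3HP: (30.375 − 2.92)/2700 = 10.2/1000, against 11.25. The ratio stays at 0.50.

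**Effect on the rate ratio, if the early effect differs (assumption).** Let f be the early share of 24 months. The all-event RR is f × early RR + (1 − f) × 0.5.

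- RR 1.0 for 12 weeks: f = 12/104.36 = 0.115, so 0.115 × 1.0 + 0.885 × 0.5 = 0.557. With those 12 weeks' events removed: 0.50.
- If only the events of the first 10 weeks are removed: (2 × 1.0 + 92.36 × 0.5)/94.36 = 0.51.
- Early RR 0.75 for 12 weeks: 0.529 against 0.50.
- Early RR 0.5: no shift.

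**Later follow-up.** By Table 3, a case diagnosed at Month 8 has had the weekly visits and one four-monthly visit to keep. An event-free participant must also keep Months 12, 16, 20 and 24, with chest x-rays at 12 and 24. This selection favours keeping cases, so it pushes rates up, against the direction of the early-case loss. The documents give no attendance figures from which to size it.

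**The case against.** The strongest reply is that this is an ambiguity in a summary. The Statistical methods section defers detail to the SAP, which is not shown and may say which visits count, how violations are judged and when per-protocol time starts. The 16-week limit is a dosing criterion and the window a visit criterion. Section {11c} re-anchors later follow-up to the last treatment date, so later visits of someone who restarted may well be in window. All of that is fair. But the exclusions are stated in the article rather than left open, a SAP that follows them inherits the problem, and re-anchoring does not say whether the missed weekly visits themselves count.

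A reader might infer stronger conclusions that the documents do not support:

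- *Every on-treatment TB case is lost.* No: a case diagnosed after dose 11 and before dose 12 meets the completion rule. Stopping also turns on a clinician's diagnosis warranting treatment, not on the endpoint algorithm.
- *The 16-week allowance has no effect.* No: the same definition serves as the treatment-completion secondary outcome.
- *The per-protocol set will be small.* That depends on in-window probabilities that the documents do not give.
- *The rate ratio is shown to be biased.* Removing early cases leaves it unchanged under a constant RR, and no between-arm direction is established for the follow-up exclusions.

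It can also be said that any set chosen by doses taken remains selected after randomisation. That stands, and no rewording removes it.

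**Conclusion.** The point holds in a limited form. Read literally, the window exclusion conflicts with the restart rule and the 16-week limit, and these passages must be reconciled. The completion rule removes TB cases treated before dose 11: 5.8 to 6.5 placebo and 2.9 to 3.2 3HP events at planning rates, roughly 10% of 24-month events. If time runs from randomisation, which the article does not state, both absolute rates fall by about 10% on this account. Bias in the rate ratio needs an early effect that differs from the later one. The move from 0.557 to 0.50 is an illustration under an assumed complete absence of early effect, not an estimate. The follow-up exclusions add selection on the outcome, of unknown size. The ITT primary analysis, the sample size and the primary conclusion are unaffected. It is worth correcting before unblinding, because the wording allows more than one per-protocol set.

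**What to change.** In Analysis populations, section {20c} and the SAP:

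1. Define the per-protocol set by eligibility and the dosing criterion as already stated.
2. Delete the second and third items in the bracketed list of major violations. Censor person-time at the last valid TB assessment instead, which the Poisson rate analysis already accommodates.
3. Choose one rule for early TB and state it: either keep participants who were adherent up to a TB diagnosis before dose 11, with person-time from randomisation, or start per-protocol person-time at a common landmark, week 16 after randomisation, among those TB-free then.

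The cost is wording only; no dose, visit, restart rule, sample size or primary analysis changes. The landmark option gives up all events before week 16: 60.75 × 16/104 = 9.3 placebo and 30.375 × 16/104 = 4.7 3HP, or 15% of 24-month events. That is more than the present rule loses, but it is done openly and in both arms, with the matching person-time removed. Selection on adherence remains under either option, so the result should be presented as supportive of the ITT analysis.

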#### Statistical methods for primary and secondary outcomes {20a}

The primary efficacy measure will be the ratio of TB (definite or probable) incidence rates (intervention vs control) adjusted for site (the stratification factor) using Poisson regression, reported as an efficacy estimate (1 − rate ratio), with a 95% CI and *p*-value. Deaths with definite or probable TB will be included in the primary endpoint, and only the first TB diagnosis will be included for each participant. For secondary analyses of the primary endpoint, cumulative incidence curves will be fit to estimate cumulative incidence (with 95% confidence bands) accounting for death from non-TB causes as a competing risk. Cox regression analysis will be used to estimate hazard ratios adjusting for age, sex, HbA1c, new vs known DM, body mass index, insulin use, smoking status and recent contact with TB case at baseline.

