### Assignment of interventions: allocation

#### Sequence generation {16a}

Participants will be randomised 1:1 to intervention or placebo using blocked randomisation within strata (clinical sites), with random block sizes. The randomisation list will be generated and managed by a validated module in the CASTOR database.

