#### Methods for additional analyses (e.g. subgroup analyses) {20b}

Analyses of secondary outcomes of (i) possible, probable or definite TB; (ii) TB incidence of death (all causes); and (iii) overall mortality will follow the same approach as for the primary outcome. For safety and completion of treatment outcome, we will compare the proportions of participants experiencing each event by arm using either *χ*^2^ or Fisher’s exact tests (depending on numbers of events). No formal adjustments are made for multiplicity across the secondary analyses, but results will be interpreted with appropriate caution.

Subgroup analyses will be conducted for the primary outcome, if the overall treatment effect is significant, by including interaction terms in the analyses. The pre-specified subgroup comparisons are area (Mbeya, Moshi, Uganda), age group (approximately tertiles), duration of DM (approximately tertiles), DM status (new vs known), BMI (as a continuous and categorical variable) and level of glycaemic control (HbA1c > 8%) at baseline. In addition, we will repeat the primary analysis (i) restricted to the group who are TST positive and (ii) restricted to the group who are IGRA positive.

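### Site, the randomisation stratum, is missing from the listed Cox covariates and from the safety and completion tests, although the primary model adjusts for it (minor, free to fix)

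*Protocol article*

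**What the plan says.** All references are to the protocol article.

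- **Sequence generation {16a}:** "Participants will be randomised 1:1 to intervention or placebo using blocked randomisation within strata (clinical sites), with random block sizes".
- **Statistical methods for primary and secondary outcomes {20a}, primary analysis:** the TB incidence rate ratio is "adjusted for site (the stratification factor) using Poisson regression".
- **Same section, secondary analyses of the primary endpoint:** after the cumulative incidence curves, a Cox model is to give "hazard ratios adjusting for age, sex, HbA1c, new vs known DM, body mass index, insulin use, smoking status and recent contact with TB case". Eight baseline variables are named; site is not one of them.
- **Methods for additional analyses {20b}, secondary efficacy outcomes:** the wider TB definition, TB or death, and "overall mortality will follow the same approach as for the primary outcome". These therefore carry the site adjustment.
- **Same section, safety and completion:** "we will compare the proportions of participants experiencing each event by arm using either" a chi-squared or Fisher's exact test, depending on event counts. No stratification is stated.
- **Same section, subgroups:** area (Mbeya, Moshi, Uganda) is a pre-specified subgroup factor.
- **Statistical methods, opening paragraph:** the text is described as a summary, with full details left to the SAP.

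**The concern.** When randomisation is stratified, the analysis should normally reflect the strata, and the plan accepts this for its primary model. The Cox model addresses the same endpoint and will be read beside the primary estimate. As listed, it adds eight covariates and drops site, so two things change at once.

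For completion and adverse events, blocking within site makes the arms alike in site mix. That removes between-site variation from the treatment comparison. A pooled test still counts this variation as noise, so its standard error is too large whenever the outcome differs by site. For a safety comparison, conservatism is not automatically the cautious direction, because it makes a real excess of harm slightly harder to see.

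Site differences are plausible. Recruitment is in Kampala, Moshi and Mbeya, in two countries, and the Interim analyses section says that event rates at the sites were not known when the protocol was developed.

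**Working it through.** **1. The plan's own figure.** Inputs from Sample size {14}: 22.5 cases/1000/year, i.e. 45/1000 over 2 years; RR 0.5; 90% power; one-sided 0.025 (Table 4); 10% loss.

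n per arm = [z(0.975)·√(2p̄q̄) + z(0.90)·√(p₁q₁ + p₂q₂)]² / (p₁ − p₂)², with p₁ = 0.045, p₂ = 0.0225 and p̄ = 0.03375:

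- [1.960 × 0.2554 + 1.282 × 0.2549]² / 0.0225² gives 1352 per arm, 2704 in total.
- 2704 / 0.90 = 3005, against 3000 stated. The same formula reproduces all nine cells of Table 4.

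This figure concerns the primary endpoint, whose model already contains site, so nothing below changes it.

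**2. Why an unstratified test of proportions is conservative.** With equal-sized sites and 1:1 allocation within site, the ratio of the correct null variance to the one the pooled test uses is

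r = mean of pₛ(1 − pₛ) over sites / p̄(1 − p̄).

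The true two-sided type I error of the pooled test is then 2[1 − Φ(1.96/√r)]. The article gives no site-specific rates, so all site proportions here are assumptions.

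Example, completion of 75/85/95%:

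- within-site: (0.1875 + 0.1275 + 0.0475)/3 = 0.1208
- pooled: 0.85 × 0.15 = 0.1275
- r = 0.1208/0.1275 = 0.948, so the pooled variance is about 5% too large.

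**3. Simulation.** Three equal sites, 500 per arm per site (N = 3000), 40,000 runs, two-sided 0.05, pooled chi-squared (χ²) against Mantel-Haenszel (MH) stratified by site. Power is at the odds ratio shown.

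| Assumed site proportions | r | Type I: χ² | Type I: MH | Odds ratio | Power: χ² | Power: MH |
|---|---|---|---|---|---|---|
| 80/90/95% | 0.962 | 0.044 | 0.049 | 0.70 | 0.900 | 0.908 |
| 70/85/98% | 0.901 | 0.040 | 0.051 | 0.75 | 0.773 | 0.806 |
| 5/10/20% | 0.962 | 0.046 | 0.050 | 1.35 | 0.766 | 0.779 |
| 10/20/40% | 0.913 | 0.041 | 0.050 | 1.30 | 0.822 | 0.846 |

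The formula in step 2 gives 0.046, 0.039, 0.046 and 0.040 for the four rows, in line with the simulation. Fisher's exact test was not simulated.

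**4. Effect on the TB estimate.** Assume control rates of 11.25, 22.5 and 45 per 1000/year at three equal sites, a within-site ratio of 0.5 and 2 years of follow-up. Pooled rate = mean of (1 − e^(−λT)) / mean of [(1 − e^(−λT))/λ]:

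- control: 0.05077/1.9487 = 0.02606
- intervention: 0.02581/1.9740 = 0.01308
- ratio: 0.502.

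A second route uses the ratio of marginal cumulative hazards, with rates of 10, 20 and 37.5 per 1000/year over 2.75 years. It also gives 0.502. These ratios stand in for the Cox hazard ratio without site; at event rates this low the two should be very close.

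**5. Precision for so rare an event.** Two-year risks of 20, 40 and 75 per 1000 give a within-site variance of 0.0425 against 0.0430 pooled. That is about 1.2% in variance, or 0.6% in standard error.

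**The case against.** The strongest reply has three parts.

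- **The article is a summary.** It never says that the Cox covariates are the only ones, and the SAP, which is not shown, may stratify that model by site. This stands: the list should not be read as closed. But the article is not silent here. It names particular covariates and particular tests, and as named they omit the stratum.
- **The consequence is small.** Site accounts for about 0.002 of the hazard ratio, so a visible gap between the Cox and Poisson results would not come from site. This also stands. For the Cox model, the case for adding site is consistency of specification, not bias or precision.
- **Pooled chi-squared and Fisher tests are conventional** for adverse events and completion, and the article promises caution in interpreting secondary results. That is fair as a description of practice. It does not remove the small loss of power, which a stratified test recovers without cost.

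A reader might infer that the secondary results as a whole ignore the design. The document does not support that: the wider TB outcome, TB or death, and mortality inherit the site-adjusted Poisson approach, the TST-positive and IGRA-positive analyses repeat the primary analysis, and area is examined as a subgroup factor. Nor does the omission make the tests invalid or inflate false positives; the error runs the other way.

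**Conclusion.** The point holds in a narrow form and is of low severity. The listed Cox covariates and the stated safety and completion tests leave out the stratum that the primary model includes.

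For completion and safety, the cost under the assumed spreads is a type I error of about 0.040 to 0.046 instead of 0.05 and a power loss of about 1 to 3 points. For the Cox estimate the cost is practically nil (0.500 to about 0.502). Sample size and primary power are untouched.

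The sizes rest on three equal sites, invented site proportions and two-sided testing at 0.05. Smaller site differences would shrink them towards zero. Whether the SAP already includes site cannot be judged from the article.

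**What to change.** - **Cox model:** stratify by site, or add site to the covariates, using the same definition of site as the randomisation list and the Poisson model.
- **Completion and safety:** compare proportions with a site-stratified Mantel-Haenszel test, or an exact stratified test when events are sparse. Report a site-stratified risk difference with 95% CI for each outcome.
- **If the SAP already specifies this:** align the published text with it.

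The cost is one or two sentences, settled before unblinding. It needs no extra data, participants or change in sample size.
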